**Methods and analysis:**

The OPERA project is a 13-months non-profit, multicentre clinical investigation structured in four phases. Phase 1 (month 2): focus group, involving 23 participants (10 people with PD (PwPD), 5 caregivers, 8 healthcare professionals) to explore usability, expectations and rehabilitation needs. Phase 2 (months 2–7): development of the PRoBio platform, by integrating the “Virtual Reality Rehabilitation System” (VRRS, by Khymeia Group) with the TIAGo robot (by PAL Robotics) to deliver personalized exercises to patients' cognitive profiles, while also monitoring their emotional and physiological state. Phase 3 (month 6): two living labs involving a total of 21 healthy subjects (13 volunteers and 8 rehabilitation professionals) to assess PRoBio's usability in a real setting, with emotional data collection and standardized usability questionnaires completion after use. Phase 4 (months 8–12): usability study assessing PRoBio's usability as the primary objective, involving 10 PD-MCI patients completing a 4-week cognitive rehabilitation program with pre/post clinical and neuropsychological assessments. Descriptive statistics and appropriate inferential tests (parametric or non-parametric) will be applied to usability data, pre/post intervention clinical measures, and physiological and performance data registered by the PRoBio platform (*p* < 0.05).

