**Figure 3 F3:**
[figure not shown]
Graphic representation of the Usability Study procedures and the data flow within the OPERA project. Clinical and neuropsychological data are collected at baseline (T0), and at the end of the treatment (T1). Usability data are collected at T1. T0, Baseline Assessment; T1, Follow-up Assessment; MDS-UPDRS, Movement Disorder Society—Unified Parkinson's Disease Rating Scale; PD-CRS, Parkinson's Disease-Cognitive Rating Scale; TMT, Trail Making Test; PDQ-39, Parkinson's Disease Questionnaire; GDS, Geriatric Depression Scale; GAI, Geriatric Anxiety Inventory; SUS, System Usability Scale; HUBBI, eHealth UsaBility Benchmarking Instrument; UEQ-S, User Experience Questionnaire-Short version; TAM, Technology Acceptance Model; I-UTAUT, Unified Theory of Acceptance and Use of Technology-Italian version; NASA-TLX, NASA Task Load Index; TARPP-Q, Technology Assisted Rehabilitation Patient Perception Questionnaire.

*Outcome measures*.

Primary outcome: usability of PRoBio assessed by SUS (34).

Secondary outcomes:

Specific aspects of usability of digital health services such as trust, safety, and information quality, measured with the HUBBI (35). User experience, including pragmatic and hedonic quality, measured with the UEQ-S (36) and with the TARPP-q (52). Technology acceptance explored by the TAM (37) and the I-UTAUT (40). Cognitive workload during interaction assessed with the NASA-TLX (41).Acceptability of the PRoBio platform and compliance with the treatment among patients with PD-MCI measured by (a) the number of treatment sessions completed/number of treatment sessions planned, (b) the number of treatment weeks/total number of weeks planned.Acceptability of the PRoBio platform among rehabilitation professionals measured by (a) the mean time for wearable sensors positioning and starting of the system; (b) the number of system errors/warning; (c) the percentage of sessions' completion.Biomechanical parameters (e.g., range and speed of the patient's movement) recorded by the RGB-D camera, and psychophysiological parameters (e.g., respiratory rate—RR, HR, and GSC), measured through wearable sensors during the treatment sessions.PRoBio's capability to collect real-time performance data during cognitive exercises administered via VRRS assessed by the number of output files recorded by PRoBio/number of exercises per session.

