Exploratory outcome: changes in clinical (MDS-UPDRS) and neuropsychological variables (PD-CRS, Stroop Test and Trail Making Test, GDS, GAI), and quality of life (PDQ-39) between the two timepoints T0 and T1.

*Sample size*. The sample size was derived using data from Saric et al. (53), who reported a mean SUS score of 77.5 (IQR: 70–80.625) when evaluating the usability of a sensor-based interactive hand device. Assuming a 95% confidence level and a conservative margin of error of five points, the minimum required sample was 10 participants, increased to 12 to mitigate potential data loss.

Since the primary objective was to assess the system's usability, all participants underwent treatment with the platform, and no control group was enrolled.

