#### Statistical analysis

2.4.2

All statistical analyses will be conducted using Jamovi software (version 2.5, 2024) (29). The Shapiro-Wilk test will be conducted to explore the distribution of the data. Descriptive statistics will be performed on primary and secondary outcomes' measures. Continuous variables will be presented as mean (standard deviation—SD) or median (interquartile range—IQR), as appropriate, and for categorical variables, as frequencies or percentages.

Paired *t*-tests, or Wilcoxon signed-rank test, as appropriate, will be performed to assess differences in clinical, neuropsychological and quality of life measures before and after the intervention (exploratory outcome).

The significance level for all analyses will be set at *p*-value < 0.05.

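### The five-point margin for the mean SUS score is met only if all 12 patients are evaluable; with the stated minimum of 10 the 95% t-interval is about ±5.6

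*Protocol article*

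**What the plan says.** Phase 4 is a single-arm usability study. Its primary outcome is given in Section 2.4.1, under Outcome measures: "Primary outcome: usability of PRoBio assessed by SUS (34".

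The Sample size paragraph of the same section takes its input from an earlier evaluation of a hand device, which it describes as reporting "a mean SUS score of 77.5 (IQR: 70–80.625". It then states: "Assuming a 95% confidence level and a conservative margin of error of five points, the minimum required sample was 10 participants, increased to 12". The increase is an allowance for lost data. The paragraph gives neither an SD nor a formula.

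Section 2.4.2 (Statistical analysis) says of the primary outcome only that "Descriptive statistics will be performed on primary and secondary outcomes' measures", as mean with SD or median with interquartile range. It names no confidence interval, no SUS threshold and no test for this outcome.

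The Abstract describes Phase 4 as "involving 10 PD-MCI patients completing a 4-week cognitive rehabilitation program" and does not mention 12.

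**The concern.** The study has no control group and no hypothesis test on its primary outcome, so the stated precision is the only quantitative justification of its size. A reader will take from it that 10 evaluable patients give a 95% interval of ±5 SUS points and that the other two are a reserve.

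Both impressions depend on treating the SD as known. With about 10 patients the SD has to be estimated from the data, and replacing the normal quantile by the t quantile widens the interval by about 15% (2.262/1.960 = 1.154). If that matters at the stated minimum, the reserve is not a reserve.

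The input is also unclear: the centre is called a mean but is paired with quartiles, and those quartiles lie at unequal distances from it.

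**Working it through.** **Inputs from Section 2.4.1.** Confidence level 95%, taken as two-sided; margin 5 points; reference SUS 77.5 with quartiles 70 and 80.625; minimum 10, raised to 12.

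**Assumption.** No SD is stated. For normal data the interquartile range is 1.349 SD, so SD = (80.625 − 70)/1.349 = 10.625/1.349 = 7.876.

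**Step 1: reproduce the plan's figure.** With the SD treated as known, n = (z × SD/margin)² = (1.96 × 7.876/5)² = 9.53, rounded up to 10. The half-width at n = 10 is 1.96 × 7.876/√10 = 4.88, inside 5. Taking the SD as the full interquartile range gives 18, and taking it as half that range gives 5. Neither matches, so the first route is very probably the one used.

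**Step 2: allow for an estimated SD.** The half-width is t(0.975, n − 1) × SD/√n, with SD = 7.876:

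| Evaluable n | Normal quantile | t quantile |
|---|---|---|
| 10 | ±4.88 | 2.262 × 7.876/√10 = ±5.63 |
| 11 | ±4.65 | ±5.29 |
| 12 | ±4.46 | ±5.004 |
| 13 | ±4.28 | ±4.76 |

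Twelve evaluable patients in effect meet the five-point margin. Losing one takes the half-width to 5.3, and losing two takes it to 5.6.

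**Step 3: chance variation in the realised width.** If the true SD is 7.876 and the data are normal, the probability that the t-interval comes out at ±5 or narrower follows from the chi-square distribution of the sample variance. It is 37% at n = 10, 56% at n = 12 and 65% at n = 13.

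**Step 4: sensitivity to the SD.** At n = 10 the t-based half-width is 5 or less only if the SD is at most 5 × √10/2.262 = 6.99. The reference quartiles lie 77.5 − 70 = 7.5 below and 80.625 − 77.5 = 3.125 above the centre. If 77.5 were a median, each gap would suggest its own SD on a normal scale:

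| Basis | SD | t half-width, n = 10 | t half-width, n = 12 |
|---|---|---|---|
| Upper gap, 3.125/0.6745 | 4.63 | ±3.31 | ±2.94 |
| Full range, 10.625/1.349 | 7.88 | ±5.63 | ±5.00 |
| Lower gap, 7.5/0.6745 | 11.12 | ±7.95 | ±7.06 |

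These rows bound what the quoted figures allow. They are not estimates of the spread in this trial.

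**The case against.** The best reply is that the plan did nothing irregular. The normal-approximation formula is standard for precision planning, 10 is exactly what it gives, and the number actually planned is 12, where even the t-based half-width is 5.004. To call 13 the first adequate number would turn on 0.004 of a SUS point, far less than the uncertainty in the assumed SD. Little depends on the result, since the primary outcome is summarised descriptively and the Discussion already calls the sample small and the analysis preliminary. The SD and formula may also be in the full protocol, which this article condenses.

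Most of that stands, and it limits the point. It does not rescue the statement that 10 is the minimum for ±5 at 95%, because that statement is made here and holds only for a known SD.

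Four stronger readings are tempting, and the documents do not support them:

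- **That 10 is a miscalculation.** It reproduces exactly (step 1). The gap is between the normal and the t quantile.
- **That the plan wrongly calls its SD conversion conservative.** In the text the adjective describes the five-point margin. Nothing is claimed about the conversion.
- **That the true precision is about ±7 to ±8.** This uses only the lower quartile gap. The upper gap gives ±3.3 at n = 10 by the same reasoning, and both require 77.5 to be a median when the article calls it a mean.
- **That 10 and 12 contradict each other.** Section 2.4.1 labels them as a minimum and the same number after an allowance for losses. The Abstract's 10 can be read as completers. The omission of 12 there is editorial.

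**Conclusion.** The point holds in a limited form. At the SD the plan appears to have used (7.88), the five-point margin is delivered with 12 evaluable patients and missed by about 0.6 point (5.63 − 5) with the stated minimum of 10. The two patients described as cover for data loss are therefore needed to reach the margin, and no allowance for loss remains.

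This rests on three assumptions: that the SD was obtained as the interquartile range divided by 1.349, which is inferred from the match with 10; that scores are roughly normal; and that the SD in this trial will be similar to that of the reference study. The third cannot be checked from the article, and the asymmetric quartiles make any single SD uncertain in both directions.

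Severity is minor to moderate. The stated precision should be corrected because it is the only numerical basis for the sample size, but no threshold, test or decision rule depends on it.

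**What to change.** Keep the planned enrolment at 12 and revise the Sample size paragraph of Section 2.4.1 as follows:

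- State the SD and the formula used and, if the SD was derived from the interquartile range, say so.
- Replace the claim that 10 is the minimum for ±5 with the expected t-based precision: at an SD of 7.9, a 95% half-width of about ±5.0 points with 12 evaluable patients and ±5.6 with 10.
- Note that the SD is an assumption drawn from an asymmetric interquartile range, and show any sensitivity range in both directions.
- Say whether 77.5 is a mean or a median, or give the SD from the source.

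As an editorial change, give the 12 planned for enrolment alongside the 10 in the Abstract.

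The cost is a few sentences and a slightly less favourable precision statement. No further patients are needed and no analysis changes. As the article reports that the project has ended, this corrects the reported justification and does not reopen the design.

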#### Statistical analysis

2.4.2

All statistical analyses will be conducted using Jamovi software (version 2.5, 2024) (29). The Shapiro-Wilk test will be conducted to explore the distribution of the data. Descriptive statistics will be performed on primary and secondary outcomes' measures. Continuous variables will be presented as mean (standard deviation—SD) or median (interquartile range—IQR), as appropriate, and for categorical variables, as frequencies or percentages.

Paired *t*-tests, or Wilcoxon signed-rank test, as appropriate, will be performed to assess differences in clinical, neuropsychological and quality of life measures before and after the intervention (exploratory outcome).

The significance level for all analyses will be set at *p*-value < 0.05.

The data acquired from the PRoBio platform will be processed through a structured workflow. In the first stage, raw data from all sensors will be pre-processed to remove artifacts. Outlier detection will be performed using robust statistical methods to ensure data integrity. In the second stage, a comprehensive set of features will be extracted. For cardiorespiratory activity, time-domain metrics will include HR and RR. For electrodermal activity, features derived from GSR will include tonic (Skin Conductance Level, SCL) and phasic components (Skin Conductance Responses, SCR), as well as frequency and amplitude of SCRs over time windows. Data acquired from the RGB-D camera and robot sensors will be used to compute biomechanical metrics. For facial expression analysis, discrete emotional states (e.g., neutral, happy, sad, surprised) will be inferred using facial action coding systems and mapped to dimensional descriptors such as valence and arousal. For all extracted features, descriptive statistics will be computed across sessions and participants. These metrics will be used both for individual-level profiling and for group-level comparisons in subsequent inferential analyses. The data will be segmented into three predefined time windows within each session, namely baseline, active interaction, and recovery, to facilitate intra-session comparison. Subsequent statistical analyses will be produced by the data distribution and will include both parametric and non-parametric tests. Furthermore, to investigate the interaction and combined effects of multiple variables (e.g., interaction duration and the participant's emotional state), linear mixed models (LMMs) or repeated measures analysis of variance (RMANOVA) will be employed. These models will facilitate the incorporation of within-subject and between-subjects factors. Statistical significance will be set at *p* < 0.05. Where relevant, corrections for multiple comparisons will be implemented using the Bonferroni method and the False Discovery Rate (FDR) approach.

## Discussion

3

The present methodological paper outlines the step-by-step procedures adopted into the development and preliminary testing of a novel, bio-cooperative rehabilitation platform (PRoBio), designed to deliver adaptive cognitive training tailored to the cognitive and emotional profiles of individuals with PD-MCI. Additionally, the methodology of the usability study in PD-MCI patients undergoing cognitive training with PRoBio is presented.

The OPERA project focuses on cognitive interventions in PD-MCI, a condition that significantly affects attention, executive functions, memory, and visuospatial abilities (3, 5). To address the limitations of conventional rehabilitation, often lacking personalization, ecological validity and long-term adherence, the project adopts innovative, engaging, and technology-based solutions, as suggested in recent reviews (8, 9).

As a core component of this approach, the OPERA project first leverages the advantages of VR-based technology, which allows the creation of immersive or non-immersive, interactive, and customizable training environments (54, 55). These features foster patient engagement and provide high ecological validity (14, 56), which are key to promoting adherence (57) and enhancing neuroplasticity through multimodal stimulation and real-time feedback (21, 26, 58).

A further key component of the PRoBio platform is adaptive human-robot interaction, which is based on the integration of VR with physiological and behavioral measurements to personalize treatment. The integration of multimodal sensing, real-time adaptation, and socially interactive robotic feedback in PRoBio has the potential to offer a more personalized and responsive form of cognitive rehabilitation, tailored to the complex needs of individuals with PD-MCI. This unified, patient-centered system will henceforth offer a scalable, ecologically valid alternative to traditional rehabilitation, which will be particularly well-suited to early and sustained cognitive interventions in neurodegenerative disease.

Beyond its methodological and technological innovation, PRoBio carries relevant clinical and translational implications when compared with existing cognitive rehabilitation approaches adopting innovative technologies.

To the best of our knowledge, current robot-aided interventions in PD primarily deliver motor training with only secondary cognitive involvement (59, 60), whereas PRoBio explicitly targets cognitive–executive mechanisms through performance-adaptive, goal-oriented tasks. This represents a conceptual shift from movement-assisted to cognitive-based rehabilitation. Furthermore, PRoBio is designed to interpret biosignals as indicators of emotional and attentional states, thus allowing it to adjust not only task parameters but also the type and timing of feedback. PRoBio, hence, extends the paradigm of bio-cooperative interaction to encompass cognitive and affective domains. This feature has the potential to enhance engagement and adherence, two domains frequently impacted by apathy and variability in motivation in PD-MCI.

The rationale supporting PRoBio methodology could be found in recent clinical findings demonstrating that a personalized, multidisciplinary, and multimodal rehabilitation pathway integrating VR, robotics, and telerehabilitation produced significant improvements in cognitive and emotional functioning in patients with PD. This approach is not only effective but it is also highly usable, well-received by patients, and has the potential to enhance engagement and adherence. Adaptability through task adjustment, feedback, and progression monitoring, is proposed as a crucial determinant of usability and cognitive benefit (61). In line with the evolving literature, recent contributions highlighted the importance of evaluating not only motor and cognitive outcomes but also the psychosocial experience of technology use in neuromotor rehabilitation (62). PRoBio, hence, operationalizes principles of personalization and feedback adaptivity within a bio-cooperative closed-loop architecture to provide a data-driven, adaptive, and physiologically informed cognitive training.

Most importantly, the OPERA project proposes a cutting-edge approach that reflects the latest advancements in the field. According to human-centered design methodology, the development of the PRoBio platform has prioritized the understanding of the needs, preferences, and usability for the direct end users. Specifically, to ensure stakeholders' involvement, a PRoBio pre-development Focus Group and post-development Living Labs were conducted. An iterative process has been adopted: (i) the co-design of the platform based on structured focus groups with clinicians, caregivers, and patients; (ii) the technical integration of robotic, virtual, and physiological modules into a unified architecture; (iii) the living lab evaluation of system usability with healthy participants to refine interaction modalities; and (iv) the usability and exploratory efficacy assessment in individuals with PD-MCI.

The focus group has been conducted prior to any technical implementation (28). It has served as an initial step to explore the perspectives of PwPD, their caregivers, and healthcare professionals. Structured questionnaires have been used to investigate the perceived usability, value, and functional expectations of the future PRoBio platform. The purpose of this phase was to gather preliminary insights to inform the system's conceptual and functional design.

The Living Labs were intended to assess the usability of the PRoBio platform in a group of healthy participants, prior to assess its usability in PD-MCI patients. As the OPERA project focuses on a frail and potentially vulnerable population of patients, the Living Lab approach was appropriate for the preliminary testing and development of healthcare innovations in real-life care settings, as recommended by Zipfel et al. (63). Furthermore, the current literature supports this user-centered approach with aging populations to co-create effective and user-friendly health solutions (64). The active involvement of stakeholders (i.e., rehabilitation professionals and healthy volunteers) aimed to ensure that the platform was aligned with real-world needs and to promote its adoption in clinical practice. Based on the feedback gathered from Phases 1 and 3, a refined version of PRoBio has been developed. This staged approach ensured that potential technical issues could be identified and addressed without burdening vulnerable clinical populations. The last phase of the OPERA project (Phase 4. Usability study) specifically included individuals with PD-MCI, thus allowing the evaluation of usability in real-world rehabilitation contexts, and preliminary assessment of cognitive and functional outcomes.

Finally, the decision to alternate cognitive training protocols using an ABAB pattern was made to foster patients' compliance. The two protocols are balanced, allowing patients to train the same cognitive domains over the 4-week intervention without losing interest in the proposed tasks.

Some limitations should be acknowledged. The Living Labs involved a relatively small sample of healthy volunteers and healthcare professionals, which limited generalisability. However, this is consistent with the methodology of the Living Lab, where formal sample size calculation is not required (42). The absence of patients with PD-MCI may have reduced ecological validity, since healthy participants cannot fully reflect the challenges faced by individuals with motor and cognitive impairments. This choice was nonetheless intentional, as the Living Labs served as a preparatory step before the clinical testing. The subsequent phase of the OPERA project includes a clinical study on PD-MCI patients to directly evaluate usability, acceptability, and clinical applicability.

The Usability Study also presents some limitations. First, it involves a relatively small sample size of PD-MCI patients, limiting generalisability. However, this should be sufficient to conduct a preliminary usability analysis of the first refined PRoBio version. According to user-centered design, this version of the platform will undergo further refinement based on the results from the usability study in the clinical setting. In addition, patient-specific factors such as apathy, fatigue, and variability in compliance may influence engagement and adherence to the training. As a matter of fact, in PD-MCI patients, apathy has been shown to be associated with poorer cognitive performance (65). Future studies should take into account motivational and emotional profiles in PwPD to ensure reliable assessment of usability, safety, and clinical outcomes of a new technology (65, 66).

